# Effectiveness of score card-based antenatal risk selection, care pathways, and multidisciplinary consultation in the Healthy Pregnancy 4 All study (HP4ALL): study protocol for a cluster randomized controlled trial

**DOI:** 10.1186/1745-6215-16-8

**Published:** 2015-01-06

**Keywords:** Pregnancy, Antenatal healthcare, Care pathway, Collaboration, Risk assessment

## Abstract

**Background:**

Promotion of healthy pregnancies has gained high priority in the Netherlands because of relatively unfavorable perinatal outcomes. In response, a nationwide study, ‘Healthy Pregnancy 4 All’ (HP4ALL), has been initiated. Part of this study involves systematic and broadened antenatal risk assessment (the Risk Assessment substudy). Risk selection in current clinical practice is mainly based on medical risk factors. Despite the increasing evidence for the influence of nonmedical risk factors (social status, lifestyle or ethnicity) on perinatal outcomes, these risk factors remain highly unexposed. Systematic risk selection, combined with customized care pathways to reduce or treat detected risks, and regular and structured consultation between community midwives, gynecologists and other care providers such as social workers, is part of this study.

**Methods/Design:**

Neighborhoods in 14 municipalities with adverse perinatal outcomes above national and municipal averages are selected for participation. The study concerns a cluster randomized controlled trial. Municipalities are randomly allocated to intervention (n = 3,500 pregnant women) and control groups (n = 3,500 pregnant women). The intervention consists of systematic risk selection with the Rotterdam Reproductive Risk Reduction (R4U) score card in pregnant women at the booking visit, and referral to corresponding care pathways. A risk score, based on weighed risk factors derived from the R4U, above a predefined threshold determines structured multidisciplinary consultation. Primary outcomes of this trial are dysmaturity (birth weight < p10), prematurity (birth <37 weeks), and efficacy of implementation.

**Discussion:**

The ‘HP4ALL’ study introduces a systematic approach in antenatal health care that may improve perinatal outcomes and, thereby, affect future health status of a new generation in the Netherlands.

**Trial registration:**

Dutch Trial Registry (
NTR-3367) on 20 March 2012.

**Electronic supplementary material:**

The online version of this article (doi:10.1186/1745-6215-16-8) contains supplementary material, which is available to authorized users.

## Background

Perinatal mortality rates in the Netherlands are higher than in other European countries and are showing a slower rate of decline
[1]. The latest confirmed statistics describe a perinatal mortality rate (deaths from 22 weeks of gestation up to 7 days postpartum) of 8.5 per 1,000 births
[2]. In addition, higher risks for adverse outcomes were found for women living in socioeconomically deprived areas, particularly in the four largest cities in the Netherlands
[3]. The adverse perinatal health outcome in the Netherlands has triggered debates and initiatives to study and intervene in possible causes for these adverse outcomes.

More than 85 percent of all causes of perinatal mortality in the Netherlands are associated with four adverse perinatal outcomes, namely congenital disorders, small for gestational age (birth weight <10th percentile for gestational age), premature delivery (birth <37 weeks), and/or a suboptimal start at birth (Apgar score <7 after 5 minutes); these are defined as the ‘Big 4’ outcomes
[4]. Poor outcomes were especially observed in deprived districts and are often associated with socioeconomic and ethnicity related risk factors such as low education, low income and poor integration into society
[5, 6].

### The Dutch system

The Dutch antenatal healthcare system is divided into three levels of care in which a distinction is made between low-risk and high-risk pregnancies. The primary level of care, antenatal health care is provided by independently practicing midwives who deliver care to pregnant women with an uncomplicated pregnancy, childbirth and the postpartum period. These women are estimated to be ‘low risk’. If complications (threaten to) occur, midwives refer the women to a gynecologist at the secondary level of care
[7]. The tertiary level of care takes place in centers for perinatology with a neonatal intensive care unit and an obstetric ‘high-care’ department. The latter is reserved for severely ill women or threatened pregnancies
[8].

### Current practice of risk selection

Current risk selection during the antenatal period focuses on medical risk factors
[9, 10]. A list of obstetric indications, for which referral from primary to secondary care is prescribed, has been composed by professionals involved in the field. On this list, the most frequently occurring medical conditions and prior obstetric complications are allocated to the different levels of care. The composition of this list was based on best evidence or best practices. Since the last update in 2003, there has been an increase in evidence of the influence of nonmedical risk factors (social status, lifestyle or ethnicity) on adverse perinatal outcomes
[11]. These risk factors are usually not considered in current risk screening practices. Moreover, it was shown that an accumulation of these risk factors can even further harm the chances of a good pregnancy outcome. This phenomenon implies that the presence of a number of smaller risk factors, rather than a single greater one, increases the risk on adverse perinatal outcomes
[4, 11, 12].

### Initiatives to improve perinatal health

To improve perinatal health, especially in socially deprived districts, the Rotterdam municipal council and health scientists of the Erasmus University Medical Centre initiated a city-wide perinatal health program ‘Ready for Baby’ in 2009
[5]. The ‘Ready for Baby’ program provided the framework for this national study. It was within this program that scorecard-based risk screening and corresponding care pathways were developed and piloted. Within the context of this program, the Rotterdam area served as a testing ground for a number of experiments, including the development and piloting of the R4U (Rotterdam Reproductive Risk Reduction) scorecard for antenatal risk screening
[13]. These former experiences were used to further improve and implement these tools in other municipalities with high perinatal mortality and morbidity in the Healthy Pregnancy 4 All study. The Healthy Pregnancy 4 All study was launched in 2011 by the Erasmus University Medical Centre in 14 municipalities in the Netherlands. It focuses on preconception care and broadened risk selection during pregnancy
[14].

In the risk assessment substudy, we will implement and investigate the Rotterdam Reproductive Risk Reduction (R4U) scorecard, corresponding care pathways and multidisciplinary consultation. This score card focuses on both medical and nonmedical risk factors, including psychological, social, lifestyle, obstetric and nonobstetric care-related risks. During the first antenatal visit, the R4U scorecard will be assessed by a midwife or gynecologist. The aim of this study is to investigate the effectiveness of this new approach in antenatal health care on perinatal outcomes.

## Methods/Design

### Outline

The study design concerns a cluster randomized controlled trial at the municipality level. Selected municipalities are randomly allocated to intervention and control groups. The intervention comprises systematic risk selection with the R4U scorecard in pregnant women at the booking visit and referral to the corresponding care pathways. A risk score, based on weighed risk factors derived from the R4U, above a predefined threshold determines consultation among community midwives, gynecologists, and other care providers, such as social workers in a multidisciplinary setting.

The study aims 1) to investigate the effectiveness of systematic approach in antenatal health care on adverse pregnancy outcomes (primarily lowering prematurity and small for gestational age outcomes) and 2) the efficacy of implementation (measured by the number of R4Us filled out by the healthcare professional, the performance of multidisciplinary deliberations and patient and healthcare professional satisfaction).

### Participants/eligibility criteria

The selection of neighborhoods is based on the presence of an elevated incidence of adverse perinatal outcomes (above both the national and municipal average). Municipalities are extracted after a selection process in which zip codes with high adverse perinatal outcomes are identified in a thorough analysis. For this analysis, data from all singleton pregnancies in the Netherlands over the period of 2000 to 2008 were obtained with permission from the Dutch Perinatal Registry (PRN)
[15]. The detailed selection process of the municipalities and geographical areas are described elsewhere
[14].

All midwives and gynecologists providing care to women living in these zip codes will be invited to participate in the Healthy Pregnancy 4 All study. All pregnant women living in these selected areas are eligible for this trial. All municipalities deal with an above-average perinatal mortality rate and many disadvantaged neighborhoods. Exclusion criteria include an acute obstetric situation during the booking visit (for example, ectopic pregnancy) and women in labor during this initial visit.

### Study design

To prevent contamination, we have randomized on the level of municipalities instead of (1) on the level of midwife practices or (2) on the level of hospitals or obstetric collaborations.

Randomization at the level of the individual patient is not possible because of contamination to a healthcare professional: a care provider will not be able to distinguish between intervention and control participants within their practice.

Many midwife practices are cooperating with hospitals in so-called obstetric collaborations (OC’s). Randomization on the level of OC’s was also not an option: hospitals are always involved in one particular OC, but midwife practices can participate in more than one OC. This is especially the case in municipalities with more than one hospital.

### Intervention and control

Use of the R4U scorecard, corresponding care pathways, and multidisciplinary consultation will be compared with conventional antenatal health care. In municipalities allocated to the intervention group, midwives and gynecologists will use the R4U scorecard during every first antenatal visit (provided that informed consent is given). The R4U scorecard consists of six domains (social status, ethnicity, care, lifestyle, medical history and obstetric history), subdivided into 70 items. The R4U scorecard is proposed to facilitate improved coordination of antenatal care through systematic and uniform risk screening for medical and nonmedical risk factors. A risk score, based on risk factors derived from the R4U, above the predefined cut-off point implies follow-up action. This follow-up action includes multidisciplinary consultation between obstetric caregivers and nonobstetric caregivers (for example, social workers) and prioritization of risk factors. For each cluster, this cut-off point will be calculated after a pilot of 50 R4U scorecards have been completed in a municipality. We strive to assess 20% of all pregnant women in this multidisciplinary setting. Healthcare professionals determine when and how to organize these meetings, with a minimum frequency of once a month. A standardized format is available to discuss a patient in such meetings. The purpose of these meetings is to assess a customized antenatal policy for each individual pregnant woman.

We developed 28 templates of care pathways for all risk factors incorporated in the R4U score card. Care pathways consist of steps a caregiver could follow to meet specific needs for pregnant women. Together with local healthcare professionals from both the perinatal care, community health services (called the GGD), and other services, these templates will be adapted to local circumstances. Local facilities, agreements, and guidelines will be incorporated. Depending on local availability, care pathways will developed for all items as presented in the R4U scorecard. These created care pathways will support the individual healthcare professional to encounter complex (non-) medical risk factors. They can also facilitate the collaboration among different healthcare professionals and professionals within the community health services.

Pregnant women in the control group will receive conventional antenatal health care. After the inclusion of 700 participants or after two-thirds of our study period (2 years), we will end the control group in a particular municipality and will start with the implementation of the R4U scorecard and corresponding care pathways. As mentioned in our introduction, several studies revealed a disadvantaged position of the Netherlands regarding perinatal mortality. For the first time, the unique organization of antenatal care in the Netherlands was openly questioned. In response, health care professionals and policy makers were urged to undertake interventions. The fact that we made municipalities aware of their perinatal health statistics and allocated them to be ‘a control’ was contradictory to ambitions to intervene, as the control status was felt to be the negligent attitude of local health authorities.

We are lenient to this aspect and will offer them the opportunity to start with the intervention after they have reached a certain amount of included subjects or at two-thirds of the way through the study. Therefore, we aim to implement and facilitate this new approach in all 14 municipalities at the end of the study period. This implies that the study design remains a parallel trial in which only pregnancy outcomes from regular antenatal health care in control municipalities will be analyzed. Pregnancy outcomes of women enrolled after the ‘cross-over’ in control municipalities (that is, women in control municipalities that were exposed the intervention) will not be analyzed for this purpose.

### Procedures, recruitment, randomization, and collection of baseline data

Randomization took place in January 2011 by an independent statistician who was not involved in executing the study. In order to decide whether matching was necessary, in each cluster, the adverse perinatal outcomes (Big 4 and perinatal mortality) were stratified according to socioeconomic status and ethnicity. Since clusters were not considerably different in terms of these characteristics, we decided that matching of clusters for socio-economic status and ethnicity was unnecessary.

As stated before, midwife practices participate in OC’s. Due to merging plans between OC’s in the north of the Netherlands, four small municipalities and one large municipality were combined and form one cluster (named Groningen). Thus, ten municipalities were randomly assigned to the intervention (n = 5) or the control group (n = 5).

In the randomization procedure, municipalities were numbered according to the expected number at risk. Hereby, we ensured that both arms of the experiment were comparable in size. Five random numbers were drawn from the uniform distribution between zero and one. If the number was below 0.5, the first of the pair would be assigned to the intervention, otherwise to the control group. The clusters Amsterdam, Tilburg, Groningen, Enschede and Nijmegen are allocated as intervention municipalities. The clusters for The Hague, Schiedam, Heerlen, Almere and Utrecht are control municipalities. The randomization scheme is available as an additional file (see Additional file
1).

The logistics are carried out in close collaboration with participating local program coordinators, midwives, gynecologists, and, if available, research midwives in the 14 participating municipalities. Eligible women will receive participant information, and they will be asked for written consent to collect data on their pregnancy outcomes by the participating healthcare professionals. These healthcare professionals will register all participating women anonymously by a study number in a web-based database. We will ask to register the 4-digit zip code, maternal age, gestational age at booking visit, and certain items of the obstetric history. All women participating in the risk assessment study within the HP4ALL study will receive either one or two questionnaires. The first questionnaire contains questions regarding baseline characteristics, such as marital status, household composition and income, education level, ethnicity, lifestyle (smoking, alcohol, and drug use), use of folic acid, medical history, and use of medication. This questionnaire will be completed around the first antenatal visit (depending on local logistics). The second questionnaire focuses on satisfaction. In this questionnaire, we will investigate patient satisfaction regarding their first antenatal visit. We compare satisfaction in participants in the intervention group with participants receiving conventional antenatal health care. This questionnaire will be completed by a selection of study participants. We will ask all participating practices/hospitals to distribute this questionnaire in a predefined time period of 3 months to all study participants having their third antenatal visit. This visit is before the so-called 20-week ultrasound. With this timing, we try to avoid bias in answering the questionnaire due to outcomes resulting from this ultrasound.

To provide baseline characteristics from participating healthcare professionals, an interview will be performed with one healthcare professional from each participating midwifery practice and hospital. In this structured interview, we will collect data on the number of patients and employees, the current use of risk-selection instruments, collaboration with hospitals and (other) midwifery practices in OC’s, and work processes in their antenatal healthcare (for example, counseling for prenatal screening, or ultrasound facilities). This will be repeated at the end of the study. We will use the Relational Coordination survey to measure the coordination performance of healthcare professionals. Gittell’s theory of Relational Coordination has been developed for measuring coordination performance among different professions. The healthcare professionals will be surveyed about their communication and relationships with other healthcare professionals during the antenatal phase. This will allow us to observe the effect of our intervention on the coordination performance of healthcare professionals
[16]. Table 
1 provides an overview of the planned assessments within the risk assessment substudy including variables, methods and outcomes.

**Table 1 Tab1:** **Planned assessments of the risk selection experiment: variables, methods and outcomes**

Patients		
Variables	Methods	Outcomes
1. INTERVENTION GROUP		
Nonmedical risk factors: 39 items from the risk scorecard, categorized into the domains of social, ethnicity, care, and lifestyle.	R4U scorecard + registration form ‘Obstetric history’	Primary outcomes:
		- Preterm birth
		- Small for gestational age
Medical risk factors: 30 items from the risk scorecard, categorized into the domains of general history and obstetric history	Questionnaire ‘Baseline characteristics’	Secondary outcomes - Undetected small for gestational age and unexpected preterm births (babies born in the first level of care)
Baseline characteristics: Age, zip code, ethnicity, onset of care, household composition, family income, employment, education level, smoking, alcohol, drugs, folic acid use, medication use, pre-existing chronic diseases, and sexually transmitted diseases.	Case Record Form ‘pregnancy and delivery data’	- Prevalence of risk factors
		- Risk accumulation
		- Involved healthcare professionals during pregnancy
		- Detection and prevention of impaired growth and preterm birth during pregnancy
		- Perinatal mortality
		- Congenital anomalies
		- Delivery modus
		- Place of delivery
2. CONTROL GROUP		
Baseline characteristics: Age, zip code, ethnicity, onset of care, household composition, family income, employment, education level, smoking, alcohol, drugs, folic acid use, medication use, pre-existing chronic diseases, and sexually transmitted diseases.	Registration form ‘Obstetric history’	- Asphyxia
	Questionnaire ‘Baseline characteristics’ Case Record Form ‘pregnancy and delivery data’	- Neonatal admission
		- Maternal morbidity (such as pre-existing chronic disease, pregnancy complications, positive booking bloods), and maternal mortality.
Patient satisfaction in both groups	Questionnaire ‘Patient experiences during the first antenatal visit’	- Which topics were discussed (10 examples)?
		- What was your experience?
		- Do you think this was important to ask?
**Care providers**		
**Variables**	**Methods**	**Outcomes**
General characteristics participating midwives practices and hospitals in both groups	Interview-based questionnaire	- Current status number of patients and employees
		- Use of risk selection instruments
		- Collaboration with hospitals and (other) midwifery practices
		- Work processes (for example, counseling for prenatal screening, or ultrasound facilities)
Care provider satisfaction in both groups	Questionnaire	- Feasibility
		- Efficacy of implementation
		- Collaboration
		- Continuation of intervention

### Outcome

The primary outcomes are small for gestational age, preterm birth, and efficacy of implementation. Small for gestational age is defined as birth weight below the 10th percentile for gestational age. Preterm birth is defined as birth before 37 weeks of gestation.

Efficacy of implementation will be measured by the number of R4Us completed by the healthcare professional against the number of booking visits, the development and use of care pathways, actual performed multidisciplinary consultations, and patient and healthcare professional satisfaction. Primary outcomes, except for patient satisfaction, will be recorded by healthcare professionals or the project team after delivery on case record forms in an electronic database.

Secondary outcomes are perinatal mortality (from the 22th week of gestation until 7 days postpartum), undetected small for gestational age and unexpected preterm births (babies born in the first level of care), and prevalence and accumulation of medical and nonmedical risk factors.

Other outcome parameters are: detection and prevention of impaired growth and preterm birth during pregnancy, delivery modus, place of delivery, involved healthcare professionals, congenital anomalies, neonatal admission, asphyxia, maternal morbidity (such as pre-existing chronic disease, pregnancy complications, and positive booking bloods) and maternal mortality.

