### Statistics

#### Sample size

The sample size is determined by focusing on the primary objective of the trial: the effectiveness of systematic antenatal screening on adverse small for gestational age (<10th percentile) and preterm birth (gestational age below 37 weeks). In this cluster-randomized trial, sample size depends on (1) the average risk of small for gestational age and preterm birth without the intervention (π_0_); (2) the expected effect of the intervention (π_1_); (3) the inflation factor reflecting the partial similarity/dependency of women’s outcomes or responses within the same cluster; (4) the α; and (5) power (1-β) of the test.

Based on data from the Dutch perinatal registry
[15], the average prevalence in our selected zip code areas in the years 2000 to 2008 was 16.7%. In the intervention group, we expect a prevalence of 13% at the end of the study period. The average prevalence of both primary outcomes in the Netherlands was 12% for the years 2000 to 2008
[15], and we expect a decline towards this prevalence during our study period. The inflation factor was estimated to be 2.06
[17]. This factor reflects the design effect of a cluster trial, and takes into account the degree of similarity among responses within a cluster. With five municipalities in each group (a total of ten clusters) and an alpha of 0.05 (two-sided test), 7,000 participants (3,500 per arm) should provide power in excess of 80%. This means 700 women are needed per cluster. It is assumed that a difference of 150 to 200 participants between the larger and smaller clusters has no implications for the outcome
[17].

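### The stated power rests on one unlabelled prevalence pair for small for gestational age and preterm birth together, but the two are separate primary outcomes and power is not established for either alone

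*Protocol article*

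**What the plan says.** In the protocol article, the Outcome section states: "The primary outcomes are small for gestational age, preterm birth, and efficacy of implementation". Each clinical outcome has its own definition: "Small for gestational age is defined as birth weight below the 10th percentile for gestational age" and "Preterm birth is defined as birth before 37 weeks of gestation". The Abstract and Table 1 also list the two separately. No section names a composite of them as an outcome.

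The Sample size section works with a single control risk, described as "the average risk of small for gestational age and preterm birth without the intervention". It gives one value for it: "the average prevalence in our selected zip code areas in the years 2000 to 2008 was 16.7" per cent. The target is also one value: "In the intervention group, we expect a prevalence of 13% at the end of the study period". The national comparator is one value too: "The average prevalence of both primary outcomes in the Netherlands was 12" per cent. From these, with a design effect of 2.06, ten clusters and a two-sided alpha of 0.05, the section concludes that "7,000 participants (3,500 per arm) should provide power in excess of 80" per cent.

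The Data analysis section plans multilevel logistic regression for the difference in SGA and preterm birth. It does not say whether this is one model for a combined outcome or one model per outcome.

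**The concern.** A power statement belongs to a specific outcome, effect and test. Here two clinical primary outcomes are named, but only one prevalence pair is given, with no statement of what it measures. If it is the prevalence of SGA and/or preterm birth, each outcome on its own is rarer than 16.7%, and the same relative effect is harder to detect in a rarer outcome.

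Two things are at stake. A null result on SGA or on preterm birth could be read as evidence of no effect from a trial with over 80% power, when that power was calculated for something else. And what counts as a positive trial depends on whether the decision rests on a composite, on either outcome or on both. The stated power cannot be matched to that decision until the quantity is identified.

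**Working it through.** **Inputs from the Sample size section.** Control prevalence p0 = 0.167; intervention prevalence p1 = 0.13; n = 3,500 per arm; design effect 2.06; two-sided alpha 0.05. Derived: effective n = 3,500 / 2.06 = 1,699 per arm; difference = 0.037; risk ratio = 0.13 / 0.167 = 0.778.

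**Formula.** Power = Φ[(d − z·SE0) / SE1], where d = p0 − p1, SE0 = √(2·p̄(1 − p̄)/1,699), p̄ = (p0 + p1)/2, SE1 = √((p0(1 − p0) + p1(1 − p1))/1,699), and z = 1.96 at alpha 0.05.

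**Step 1: the plan's own figure.** SE0 = 0.01220 and SE1 = 0.01218. Then (0.037 − 1.96 × 0.01220)/0.01218 = 1.07, so power = 85.9%. Equivalently, 80% power needs 1,449 per arm before inflation, and 1,449 × 2.06 = 2,985 after it. The claim of more than 80% reproduces for this pair.

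**Step 2: what the pair can describe.**
- *SGA and/or preterm birth.* This fits the use of one figure for both outcomes. As an illustration, an independent split of 10% and 7.4% gives a union of 1 − 0.900 × 0.926 = 16.7%. Applying the risk ratio of 0.778 to each gives 7.78% and 5.76%, and a union of 1 − 0.9222 × 0.9424 = 13.1%, close to the planned 13%.
- *The mean of two prevalences.* The two would then have to sum to 2 × 16.7% = 33.4%.
- *Each outcome at 16.7%.* SGA below the 10th percentile is near 10% in a reference population by construction. The study areas were selected for poor outcomes, so a higher value there is not excluded.

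The first reading is the most plausible, but it is an inference.

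**Step 3: power for a single outcome at the same relative reduction.** The article gives no component prevalences, so those below are assumptions. The design effect is kept at 2.06.

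| Assumed control prevalence | At risk ratio 0.778 | Power, alpha 0.05 | Power, alpha 0.025 |
|---|---|---|---|
| 14% | 10.9% | 78% | 69% |
| 12% | 9.3% | 71% | 61% |
| 10% | 7.8% | 62% | 51% |
| 8% | 6.2% | 52% | 41% |
| 6% | 4.7% | 41% | 30% |

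For example, at 10%: d = 0.02216, SE0 = 0.00977, SE1 = 0.00976, and (0.02216 − 1.96 × 0.00977)/0.00976 = 0.31, so power = 62%. Power crosses 80% between 14.5% (79.8%) and 14.6% (80.1%).

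**Step 4: the same absolute drop instead.** A fall of 3.7 points in the single outcome gives 91% power at 14%, 98% at 10% and over 99% at 6%. The relative reductions needed are 3.7/14 = 26% up to 3.7/6 = 62%.

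**Step 5: dependence on the success rule.**
- *Either outcome suffices, each tested at 0.05:* familywise error is 1 − 0.95² = 9.75% if the tests are independent, and 9.1% at correlation 0.5.
- *Both must succeed:* there is no inflation, but under the illustrative split, power is 0.62 × 0.49 = about 30% if the tests are independent.
- *Alpha of 0.025:* even the 16.7% to 13% pair gives 78.6%.

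All figures use the normal approximation. The effect of having only ten clusters is a separate matter and is left out here.

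**The case against.** The strongest reply is that the article never calls 16.7% a combined prevalence, so the low component powers rest on assumed inputs. The national figure adds doubt: if SGA is about 10%, a national union of 12% leaves only about 2 points for preterm births that are not SGA. Power would also be ample if each outcome fell by 3.7 points. This stands in part. The combined reading is an inference, and the component powers are conditional. But the doubt about the label is itself the problem, and the equal-absolute-drop case sits badly with the combined reading. If the union falls by 3.7 points and each component also falls by 3.7 points, the overlap must fall by 3.7 points as well. Under the illustrative split, the overlap is only 0.10 × 0.074 = 0.7%.

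Three stronger readings are tempting, and the document supports none of them.
- *The stated power applies to none of the outcomes.* This would need component prevalences and effects that are not given. If each outcome really were at 16.7% and fell to 13%, the 85.9% would hold for each at alpha 0.05.
- *Two tests will be run unprotected at 5%.* Alpha is stated once, neither the number of models nor a success rule is given, and a multiplicity rule may sit in an analysis plan that is not shown. Its absence here is not an error.
- *The calculation wrongly omits implementation.* The Sample size section confines itself to SGA and preterm birth, and the Outline makes implementation a second aim with its own measures. Patient satisfaction, one of those measures, is to be compared between the groups.

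An unseen analysis plan does not settle the main point, because the article itself states both the primary outcomes and the power, and the two do not correspond.

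**Conclusion.** The point holds in a limited form. The protocol names two separate clinical primary outcomes and supports its power with one unlabelled prevalence pair. The calculation is arithmetically sound for that pair, but more than 80% power is not established for SGA alone or for preterm birth alone.

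The size depends on assumptions. With the planned relative reduction and a design effect of 2.06 for each outcome, any control prevalence below about 14.6% gives less than 80% power, and the range from 12% down to 6% gives 71% down to 41%. A larger relative reduction in each component would restore power, but the article does not claim one. The inflation to 9.75% arises only if success on either outcome counts, each is tested at 0.05 and the tests are independent. It is a consequence to guard against, not something that the protocol prescribes.

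**What to change.** First, state in the Sample size section what 16.7%, 13% and 12% each measure. Then, before outcomes are analysed, take one of two routes.

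1. If the figures describe SGA and/or preterm birth, make that composite the single clinical primary outcome and report the two components separately. The existing calculation then supports it, with no extra women or data. The cost is a documented amendment of the primary outcome in a registered trial that is already recruiting. The primary result would also no longer distinguish growth from prematurity.
2. If both outcomes stay primary, give the control prevalence, expected effect and restated power for each. State either Holm's procedure (if success on either counts) or a rule that both must succeed. This leaves the named outcomes unchanged and costs only text and analysis work, but the stated power may be less favourable. At the planned relative reduction, 80% power for a 10% outcome at alpha 0.05 would need about 5,335 women per arm, against the 3,500 planned.

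Under either route, the Data analysis section should say which model or models carry the primary conclusion.
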